### Data safety monitoring

The DSMC will meet every 6 months after study initiation to review toxicity outcomes, but will also be notified in-between meetings if more than 2 grade 5 treatment-related toxicities occur within the first 7 patients enrolled to any cohort, or for any subtype of ILD regardless of cohort.

The dose will be de-escalated if 2 or more of the first 7 patients in a specific cohort or with a specific ILD subtype experience grade 5 treatment-related toxicity within 6 months of treatment. For example, if 2 of the first 7 patients in cohort III experience grade 5 toxicity within 6 months of treatment, then the dose will be de-escalated for all future patients in cohort III. Similarly, if 2 of the first 7 patients with CTD-ILD experience grade 5 toxicity within 6 months of treatment, then the dose will be de-escalated for all future patients with CTD-ILD.

After each de-escalation, if 2 of the next 7 patients in that cohort develop grade 5 toxicity within 6 months of treatment, then de-escalation will be repeated. The dose will be de-escalated to 50 Gy in 10 fractions, then 45 Gy in 15 fractions, using the same dose prescription techniques as described above. After 45 Gy in 15 fractions, if further de-escalation is needed then that cohort will be closed.

Using binomial distribution modelling, the performance characteristics of this approach are displayed in Table 6.

**Table 6 Tab6:** Probability of dose de-escalation based on true risk of death in a given patient cohort

True Risk of Death in a Given Cohort	Probability of De-Escalation for that Cohort
0.08	10%
0.15	28%
0.30	67%

^a^At risk levels higher than 30%, which are thought to be extremely unlikely, dose de-escalation probabilities rise further, and chances of de-escalation within the first few patients are very high

If de-escalation occurs for a certain cohort, then further patients enrolled in that cohort will be treated with de-escalated doses but will not count towards the overall accrual goal (i.e. there will be 39 patients treated with 50 Gy in 5 fractions, although ALL patients treated will be followed for outcomes and reported). Final results will be stratified by dose level: they will be presented for all patients, patients treated with the target dose of 50 Gy in 5 fractions, and for patients treated at de-escalated doses.

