**Methods:**

ASPIRE-ILD is a single-arm Phase II prospective study. The accrual target is 39 adult patients with T1–2N0M0 non-small cell lung cancer with co-existing ILD who are not candidates for surgical excision. Pathological confirmation of diagnosis is strongly recommended but not strictly required. Enrolled patients will be stratified by ILD-related mortality risk. The starting SABR dose will be 50 Gy in 5 fractions every other day (biologically effective dose: 100 Gy_10_ or 217 Gy_3_), but the radiation dose can be de-escalated up to two times to 50 Gy in 10 fractions daily (75 Gy_10_ or 133 Gy_3_) and 45 Gy in 15 fractions daily (58 Gy_10_ or 90 Gy_3_). Dose de-escalation will occur if 2 or more of the first 7 patients in a cohort experiences grade 5 toxicity within 6 months of treatment. Similarly, dose de-escalation can also occur if 2 or more of the first 7 patients with a specific subtype of ILD experiences grade 5 toxicity within 6 months of treatment. The primary endpoint is overall survival. Secondary endpoints include toxicity (CTC-AE 4.0), progression-free survival, local control, patient-reported outcomes (cough severity and quality of life), rates of ILD exacerbation and changes in pulmonary function tests/high-resolution computed tomography findings post-SABR.

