### Causality of pre-specified toxicity endpoints

Any Grade 3–5 toxicity listed in Table 4 will **automatically** be considered to be possibly, probably or definitely related to treatment, unless there is clear evidence that the adverse event is unrelated or unlikely to be related. The latter instance may occur, for example, in the case of a cardiac event in a patient with an upper lobe tumor and negligible heart dose, or esophageal issues in a patient who received negligible esophageal dose. The final decision will be made by the members of the data safety monitoring committee (DSMC). See below for causality definitions.

**Table 4 Tab4:** Pre-specified adverse events

Structure	Adverse Event
Cardiac and Pericardial	• Acute coronary syndrome
	• Aortic valve disease
	• Atrial fibrillation
	• Atrial flutter
	• Atrioventricular block
	• Conduction disorder
	• Constrictive pericarditis
	• Heart failure
	• Left ventricular systolic dysfunction
	• Myocarditis
	• Pericardial effusion
	• Pericardial tamponade
	• Pericarditis
	• Cardiomyopathy
	• Cardiac disorders-others
Gastrointestinal	• Dyspepsia
	• Dysphagia
	• Esophageal fistula
	• Esophageal hemorrhage
	• Esophageal necrosis
	• Esophageal obstruction
	• Esophageal stenosis
	• Esophageal perforation
	• Esophagitis
Pulmonary/mediastinal	• Atelectasis
	• Bronchial fistula
	• Bronchial obstruction
	• Bronchopleural fistula
	• Bronchopulmonary hemorrhage
	• Dyspnea
	• ILD or IPF exacerbation
	• Pneumonitis
	• Tracheal/Pulmonary fistula
	• Tracheal stenosis
	• Mediastinal hemorrhage
	• Pulmonary disorders-others

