### Immediately reportable adverse events

Any grade 4 or 5 adverse reaction that is definitely, probably, or possibly the result of experimental treatment (i.e. radiotherapy) must be verbally reported to the Principal Investigator and Coordinating Centre within 24 h of discovery, and to the approving REB if necessary as per their reporting guidelines.

Local and non-local SAEs will be reported to the applicable REB as per their reporting guidelines. All **serious**, **unexpected** adverse events or reactions **regardless of causality** will be reported within **7** days of discovery to the pertinent REB, or as required as per the REB guidelines.

Note: conditions that are NOT related to protocol treatment or baseline Interstitial Lung Disease are not considered a SAE in this protocol.

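### The DSMC is notified between meetings only at 3 or more grade 5 toxicities in the first 7 patients, but the dose is de-escalated at 2 or more

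*Protocol article*

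**What the plan says.** The protocol article, Data safety monitoring, has the DSMC meet every 6 months to review toxicity. Between meetings the committee "will also be notified in-between meetings if more than 2 grade 5 treatment-related toxicities occur within the first 7 patients" of any cohort, or of any ILD subtype regardless of cohort.

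The following paragraph sets the dose rule: "The dose will be de-escalated if 2 or more of the first 7 patients in a specific cohort or with a specific ILD subtype" have a grade 5 treatment-related toxicity within 6 months. The worked examples sit exactly at the boundary. One reads "if 2 of the first 7 patients in cohort III experience grade 5 toxicity within 6 months of treatment", and the other uses 2 of the first 7 patients with CTD-ILD. The abstract agrees: "Dose de-escalation will occur if 2 or more of the first 7 patients in a cohort experiences grade 5 toxicity".

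Two other sections bear on who learns of a death and who judges it:

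- Causality of pre-specified toxicity endpoints presumes that grade 3–5 events listed in Table 4 are related "unless there is clear evidence that the adverse event is unrelated or unlikely to be related". It leaves the final decision to the DSMC and gives no timing.
- Immediately reportable adverse events says that related grade 4 or 5 events "must be verbally reported to the Principal Investigator and Coordinating Centre within 24 h of discovery", and go to the ethics board if necessary. The DSMC is not named.

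**The concern.** Two adjacent paragraphs set different thresholds for the same event, the same first 7 patients and the same groupings. The committee alert sits one event above the action it should accompany, and the article gives no reason for that order.

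It matters because the dose rule counts treatment-related deaths, and relatedness is the hard judgement in this trial. Rationale for primary endpoint and study design says that deaths from ILD and from pneumonitis are difficult to tell apart, and that misattribution could wrongly lower the dose. The DSMC is given the final call on that question. With exactly 2 deaths among the first 7, one of two things can follow:

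- The centre changes the dose for all later patients in that cohort or subtype without timely DSMC review of relatedness. Later patients in a de-escalated cohort also no longer count toward the 39.
- The centre chooses to wait for DSMC adjudication, and the dose change can then be delayed until the next 6-monthly meeting.

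**Working it through.** **Inputs, all from Data safety monitoring.** Seven patients; de-escalation at X ≥ 2; notice at X > 2, that is X ≥ 3; true risks in Table 6 of 0.08, 0.15 and 0.30; binomial model, as the article states.

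**Formulas.** With X ~ Binomial(7, p):

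- P(X = 0) = (1 − p)^7
- P(X = 1) = 7p(1 − p)^6
- P(X = 2) = 21p²(1 − p)^5
- P(X ≥ 2) = 1 − P(X = 0) − P(X = 1)
- P(X ≥ 3) = P(X ≥ 2) − P(X = 2)

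**Step 1: reproduce Table 6 with 2 or more.**

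- p = 0.08: 1 − 0.5578 − 0.3396 = 0.1026 (Table 6: 10%)
- p = 0.15: 1 − 0.3206 − 0.3960 = 0.2834 (Table 6: 28%)
- p = 0.30: 1 − 0.0824 − 0.2471 = 0.6706 (Table 6: 67%; the last digit is from unrounded terms)

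All three agree. Table 6 prints no threshold, so the alternative was tried too: 3 or more gives 0.0140, 0.0738 and 0.3529, which match none of the entries. The de-escalation trigger is therefore 2.

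**Step 2: compare the two thresholds.**

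| True risk | De-escalation met, P(X ≥ 2) | Notice reached, P(X ≥ 3) | Gap, P(X = 2) | Gap as share of triggers |
|---|---|---|---|---|
| 0.08 | 10.3% | 1.4% | 8.9% | 0.0886/0.1026 = 86% |
| 0.15 | 28.3% | 7.4% | 21.0% | 0.2097/0.2834 = 74% |
| 0.30 | 67.1% | 35.3% | 31.8% | 0.3177/0.6706 = 47% |

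At 15%, the article's own limit for acceptable treatment-related death, about three in four triggering outcomes never reach the notice threshold within the first 7 patients.

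**Step 3: look for another route to the DSMC.** The 24-hour report goes to the Principal Investigator and the Coordinating Centre, with the ethics board as needed. The causality section gives the DSMC a decision but sets no deadline and no duty to notify. The between-meeting sentence is the only expedited DSMC notice in the article, so nothing else covers the case of exactly 2.

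**The case against.** The strongest reply is that the protective action does not depend on the notice. The dose rule is worded as automatic, Table 4 events are presumed related, and related deaths reach the centre within 24 hours. The count can reach 2 and the dose can change without the DSMC. The two thresholds govern different acts, so both sentences can be obeyed as written. Of the two consequences, changing the dose before DSMC review is the cautious direction for toxicity, and delay arises only if the centre waits for an adjudication that the rule does not require. All of this stands. It limits the consequence but does not explain why the committee should be alerted later than the action threshold.

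It can also be said that Table 6 confirms only the de-escalation trigger, and that a fuller protocol or a DSMC charter may set a faster route. The first point is right: that 2 was also meant for the notice is an inference from the surrounding text, though no reason for a higher figure is given. The second does not remove the problem, because the article does not leave the threshold unstated. It states one, and that one is out of line with the rule beside it.

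Finally, changing the one phrase does not cover the repeat rule, which applies to the next 7 patients after a de-escalation, and the notice lacks the dose rule's 6-month window. Both are true. They are further gaps and do not weaken the point about the first 7.

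**Conclusion.** The concern holds: the notice threshold is wrong as written and should be corrected. When exactly 2 of the first 7 patients have a treatment-related death, the de-escalation condition is met but the article does not require that the DSMC be told before its next meeting, at most 6 months later.

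The probabilities assume independent patients with a common risk, and they describe one group of 7 in isolation, as Table 6 does. They measure how often the two thresholds part. They do not measure a delay in dose change or a number of patients exposed. The primary endpoint and its analysis are not affected. Confidence is high that the text is inconsistent; the practical consequence depends on what the centre does at 2 events.

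**What to change.** In the first paragraph of Data safety monitoring, replace *more than 2* with *2 or more*, so that the notice for the first 7 patients fires at the same count as the de-escalation rule. On the binomial figures, notice would then be reached with probability 10.3%, 28.3% and 67.1% at the three Table 6 risks, instead of 1.4%, 7.4% and 35.3%.

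The cost is one phrase in one sentence. The abstract and Table 6 need no change, and sample size, power and alpha are untouched. While the sentence is open, it would be sensible to extend the notice to the next 7 patients after each de-escalation and to state the same 6-month window, but the main correction does not depend on this.

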### Interstitial lung disease and SABR

Interstitial lung disease (ILD), also known as diffuse parenchymal lung disease, comprises a heterogeneous group of diseases characterized by a non-neoplastic, diffuse inflammatory and/or fibrotic pathology affecting the lung parenchyma, usually exhibiting a restrictive defect on pulmonary function testing with reduced gas exchange [7, 8].

ILD can be subdivided into fibrotic and non-fibrotic subtypes. Fibrotic subtypes include idiopathic pulmonary fibrosis (IPF), connective tissue disease-associated ILD (CTD-ILD), idiopathic non-specific interstitial pneumonia, hypersensitivity pneumonitis, and unclassifiable ILD. Fibrotic ILDs are characterized by reticulation, traction bronchiectasis, and frequently honeycombing on high-resolution computed tomography (HRCT). These fibrotic subtypes of ILD are the focus on this research protocol.

Patients with NSCLC and co-existing fibrotic ILD represent a high-risk group for any type of cancer treatment. Patients with ILD and NSCLC are at risk of both treatment-related toxicities and acute exacerbation of ILD [9], which can be life-threatening and even fatal. Despite the generally favorable toxicity profile of SABR, emerging data indicate that patients with pre-existing ILD are at particularly high risk of toxicity after SABR. A recent meta-analysis examined outcomes after several different treatments for early-stage lung cancer in patients with ILD [10]. Within the meta-analysis, 13 published studies (Additional file 1) assessed outcomes after SABR. Overall, the use of SABR in patients with early-stage NSCLC and pre-existing ILD was associated with a 25% risk of radiation pneumonitis (grade 3 or higher) and a 15% risk of treatment-related death. The risk may be highest in the subset of patients with IPF: SABR-related mortality was 33% in studies limited to IPF patients, and 14% in other studies that included only non-IPF fibrotic ILD, or a combination of IPF and non-IPF fibrotic ILD patients (*p* = 0.092).

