However, the true rates of toxicity likely differ from the results of this meta-analysis, as nearly all the included studies were retrospective, a wide range of doses were used, and there was substantial variability in outcomes (e.g., treatment-related death ranged from 0 to 60% across studies). There is also risk of publication bias favoring the publication studies that show remarkable results (i.e. high rates of toxicity). Compounding these limitations, attribution of toxicity to radiation is difficult, since ILD exacerbations and radiation pneumonitis may result in similar clinical presentations.

Therefore, the true rates of toxicity of SABR in fibrotic ILD patients are likely higher than in the general population, but the precise extent of toxicity remains unknown.

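### The Table 6 footnote overstates how early the de-escalation rule acts above a 30% risk of death, and dismisses such risks although the protocol cites 33% for IPF

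*Protocol article*

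**What the plan says.** Under Data safety monitoring, the protocol article de-escalates the dose "if 2 or more of the first 7 patients in a specific cohort or with a specific ILD subtype experience grade 5 treatment-related toxicity"; events count for 6 months after treatment. The rule therefore runs on ILD-GAP cohorts and, separately, on ILD subtypes; the section's own example of a subtype trigger is "if 2 of the first 7 patients with CTD-ILD experience grade 5 toxicity within 6 months of treatment".

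The performance of the rule is then given: "Using binomial distribution modelling, the performance characteristics of this approach are displayed in Table 6". The table, titled "Probability of dose de-escalation based on true risk of death in a given patient cohort", has three rows: true risks of 0.08, 0.15 and 0.30, with de-escalation probabilities of 10%, 28% and 67%.

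The footnote covers everything beyond the last row. It begins "At risk levels higher than 30%, which are thought to be extremely unlikely", says that the probabilities rise further there, and ends "chances of de-escalation within the first few patients are very high".

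The Background (Interstitial lung disease and SABR) reports from a meta-analysis that "SABR-related mortality was 33% in studies limited to IPF patients", against 14% in the other studies (p = 0.092), and that "treatment-related death ranged from 0 to 60% across studies". It adds that most of these studies were retrospective and that publication bias may favour reports of high toxicity, and concludes that the exact size of the risk is not known.

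**The concern.** The footnote is the protocol's only statement of how the safety rule behaves above 30%, and it makes two claims.

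- **Plausibility.** It puts risks above 30% almost out of question, while the Background cites a figure above 30% for IPF. Any fibrotic ILD subtype is eligible (Inclusion criteria), IPF is one of the categories assigned at central review, and the rule is applied by subtype. A 33% risk in IPF is thus a case that the rule has to cover.
- **Speed.** It says that at such risks the rule is very likely to act after only a few patients. This can be checked with the model that produced the table.

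An ethics board, a site or the DSMC relying on the footnote would expect faster protection of a high-risk group than the rule provides.

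**Working it through.** **Inputs.** Threshold of 2 events in 7 patients and the binomial model: Data safety monitoring. True risks: 0.08, 0.15 and 0.30 from Table 6; 0.33 and 0.60 from the Background; 0.40 and 0.50 as points between them.

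**Formula.** With n patients treated and true risk p, the chance that at least two have died is

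P(X ≥ 2) = 1 − (1 − p)^n − n·p·(1 − p)^(n−1).

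**Step 1: reproduce Table 6 (n = 7).**

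- p = 0.08: 1 − 0.5578 − 0.3396 = 0.1026 (stated 10%)
- p = 0.15: 1 − 0.3206 − 0.3960 = 0.2834 (stated 28%)
- p = 0.30: 1 − 0.0824 − 0.2471 = 0.6706 (stated 67%)

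All three agree, so the model and the threshold are not in dispute.

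**Step 2: the IPF figure, p = 0.33.**

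- n = 3: 1 − 0.67³ − 3 × 0.33 × 0.67² = 1 − 0.3008 − 0.4444 = 0.2548
- n = 4: 1 − 0.67⁴ − 4 × 0.33 × 0.67³ = 1 − 0.2015 − 0.3970 = 0.4015
- n = 5: 1 − 0.67⁵ − 5 × 0.33 × 0.67⁴ = 1 − 0.1350 − 0.3325 = 0.5325
- n = 7: 1 − 0.67⁷ − 7 × 0.33 × 0.67⁶ = 1 − 0.0606 − 0.2090 = 0.7304

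**Step 3: the same formula at and above the last printed row.**

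| True risk | by patient 3 | by patient 4 | by patient 5 | by patient 7 |
|---|---|---|---|---|
| 0.30 | 22% | 35% | 47% | 67% |
| 0.33 | 25% | 40% | 53% | 73% |
| 0.40 | 35% | 52% | 66% | 84% |
| 0.50 | 50% | 69% | 81% | 94% |
| 0.60 | 65% | 82% | 91% | 98% |

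**Step 4: the risk at which the early-action claim becomes true.** Solving P(X ≥ 2) = 0.80 for p gives about 0.71 for n = 3, 0.58 for n = 4 and 0.49 for n = 5. The footnote makes its claim for every risk above 0.30.

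**The case against.** The strongest reply is that this is loose wording in a footnote that no rule, sample size or analysis uses. Table 6 is right, and so is the remark that the probabilities rise further. That stands, and it limits the point to a correction of wording.

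On plausibility, the footnote gives an opinion, and the Background offers some grounds for it: retrospective studies, varied doses, possible publication bias and uncertain attribution. The 33% is a subgroup figure (p = 0.092) with no stated time window, whereas the rule counts deaths within 6 months; the 60% is the extreme of a range. Table 6 is also labelled by cohort, and an ILD-GAP cohort can mix subtypes. These are good reasons to doubt 33%. They do not make values above 30% extremely improbable when the same document says that the size of the risk is unknown and runs the rule on IPF separately.

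On speed, much depends on how many patients count as a few. If five do, the chance is 81% at a risk of 50%. At 33% it is still only 53%.

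A reader might infer more, which the documents do not support:

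- *That a high miss rate is hidden.* At 33% a 7-patient set stays silent in 27% of cases (1 − 0.7304), but the printed 67% at a risk of 30% already discloses a 33% miss rate.
- *That the rule rarely acts early.* This is too strong for 40% by the fourth patient; it usually does not.
- *That a silent trigger is taken as proof that the dose is acceptable.* No section says so. Acceptability has its own limits, including treatment-related death below 15% (Rationale for primary endpoint and study design; Statistical design and sample size), and the DSMC reviews toxicity every 6 months whether or not a trigger fires.

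**Conclusion.** The point holds as an error in the footnote, not in the table or the rule. The early-action claim is wrong as written: just above 30% the table's own model gives 25% to 40% by the third or fourth patient, and the chance by the fourth exceeds 80% only near a risk of 60%. The dismissal of risks above 30% conflicts with the Background's IPF figure and with its statement that the size of the risk is unknown.

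The figures rest on two simplifications that pull in opposite directions. They treat each outcome as known before the next patient is treated; because deaths count for up to 6 months, real action would come later in enrolment. They also describe a single trigger set; an IPF patient counts in an ILD-GAP cohort as well, so the chance that some trigger fires may be higher. The protocol gives neither the accrual rate by subtype nor the overlap, so neither effect can be sized from it.

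**What to change.** - Delete or qualify the two footnote phrases: the one on how unlikely risks above 30% are, and the one on de-escalation within the first few patients.
- Add rows to Table 6 at 0.33, 0.40 and 0.60, with de-escalation probabilities of 73%, 84% and 98%.
- Add a column for two deaths within the first 4 patients. The new rows read 40%, 52% and 82%. The existing rows read 3% (1 − 0.7164 − 0.2492 = 0.0344 at 0.08), 11% (1 − 0.5220 − 0.3685 = 0.1095 at 0.15) and 35% (at 0.30).
- State that the probabilities are per trigger set and take outcomes as known at once.
- Have the sponsor and the DSMC reconcile the footnote with the Background's figures for IPF and for the range across studies.

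The cost is a few lines of protocol text and table. It needs no extra patients or procedures, and no change to the dose or the de-escalation rule is proposed.

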## Objectives

### Primary endpoint

Overall survival: defined as time from enrollment to death from any cause

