### Procedure if lung constraints cannot be met

**The lung constraints are critically important for this study.** If one or more of the lung constraints cannot be met, even after varying the prescription isodose surface percentage between 60 and 90%, PTV coverage must then be compromised. Target coverage may be reduced until 95% of the IGTV is receiving the 95% of the prescription dose, and 90% of the IGTV is receiving 99% of the prescription dose, with the PTV covered as well as possible while respecting lung constraints.

**If the lung dose constraints still cannot be met, the patient should be treated with a 10 or 15-fraction regimen.** Such patients treated with protracted regimens due to inability to meet dose constraints will not count toward the primary analysis, but should still be followed for toxicity and outcomes. Such patients will be reported as a separate cohort.

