## Statistical considerations

### Statistical design and sample size

The primary endpoint of this study is overall survival in patients able to be treated with a dose of 50 Gy in 5 fractions, with a comparison to historical controls of untreated medically inoperable patients stage I NSCLC, which consistently have survivals of less than 1 year, as described in the Background section. Demonstration in this study that median OS after SABR is statistically greater than a historical control of < 12 months would indicate that SABR is worthwhile in this population of ILD patients, if toxicity is within acceptable limits.

A sample size of 39 patients provides >80% power to detect an OS improvement of >20% at 1 year, compared to a historical control of <50% (i.e. 70% vs. 49%), using a one-sample, one sided binomial test at the 0.05 significance level, assuming 10% dropout or loss to follow-up before one year. All cohorts will be combined for this primary analysis.

SABR will be considered worthwhile if OS is > 1 year, the risk of grade 3 or 4 pulmonary toxicity is < 35%, and the risk of treatment-related mortality is < 15%.

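### The primary survival set is fixed by events after enrolment while the survival clock starts at enrolment, so case mix, and possibly immortal time, can favour the treatment

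*Protocol article*

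**What the plan says.** All references are to the protocol article.

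- **Time origin.** Objectives, Primary endpoint: overall survival is "defined as time from enrollment to death from any cause".
- **Primary population.** Statistical design and sample size fixes it in these words: "The primary endpoint of this study is overall survival in patients able to be treated with a dose of 50 Gy in 5 fractions". All ILD-GAP cohorts are pooled, no weighting is stated, and the comparison is with a historical 1-year survival of 49%. A positive result, with toxicity inside its limits, is to mean that SABR is worthwhile in this ILD population.
- **Planning failures.** Procedure if lung constraints cannot be met: patients moved to 10 or 15 fractions "will not count toward the primary analysis" and are reported as a separate cohort.
- **De-escalation.** Data safety monitoring: the dose is lowered "if 2 or more of the first 7 patients in a specific cohort or with a specific ILD subtype" have a treatment-related grade 5 event within 6 months. Further patients in that cohort "will be treated with de-escalated doses but will not count towards the overall accrual goal", and the section spells out that "there will be 39 patients treated with 50 Gy in 5 fractions". Results will also be shown for all patients and by dose level.
- **Expected heterogeneity.** ILD severity: 3-year mortality ranges from 10% to 75% across the ILD-GAP index, and subtype and severity are hypothesised to influence radiation toxicity.

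**The concern.** Membership of the primary set depends on what happens after enrolment, by two routes.

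(a) **Case mix.** Once a group is de-escalated, its remaining places among the 39 go to patients from groups that have not had the early deaths. The mix of the primary set then depends on mortality, which is part of the primary endpoint.

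(b) **Entry to the set.** Planning failures are excluded in words. In addition, a set of patients able to be treated, together with a target counted in treated patients, can be read to leave out anyone who dies or deteriorates before the first fraction. Under that reading the remaining patients are credited with time from enrolment during which they could not have died in the analysis.

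A single-arm trial against a fixed 49% has no concurrent arm to absorb such shifts. Both routes act in the favourable direction: on the survival test and, for (a), also on the 15% limit for treatment-related death.

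**Working it through.** **1. The plan's own figures.** Inputs from Statistical design and sample size: 0.49 against 0.70, one-sided 0.05, 10% dropout.

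- Normal approximation: n = [(1.645 × √(0.49 × 0.51) + 0.842 × √(0.70 × 0.30)) / 0.21]² = 33.1, so 34. Then 34/0.9 = 37.8, so 38, close to the stated 39.
- Exact binomial with n = 39: reject at 25 or more survivors, error 0.042, power 0.836.
- Table 6, P(at least 2 of 7): 0.103, 0.283 and 0.671 at risks of 0.08, 0.15 and 0.30, matching the stated 10%, 28% and 67%.

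The arithmetic is sound. The question is which patients enter the test.

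**2. Route (a), case-mix shift.** Assumptions, not in the documents:

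- three cohorts enrolling equally, with only the cohort trigger modelled;
- 6-month grade 5 risks of 8/15/30% (the Table 6 values);
- true 1-year survival averaging 49%;
- rejection at 25 or more of 39.

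The patients who trigger de-escalation stay in the set. Results by simulation:

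| Assumed cohort 1-year survival | Type I error |
|---|---|
| 49/49/49% | about 0.04 |
| 54/49/44% | 0.05-0.06 |
| 59/49/39% | about 0.07 |
| 64/49/34% | 0.09-0.11 |

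In the last row, with deaths known at once, the mix moves from one third each to about 45/35/20%. Expected survival is then 0.45 × 64 + 0.35 × 49 + 0.20 × 34 = 52.8%, against 49%. The effect shrinks the later deaths become known: in that row the error falls to about 0.08 if 7 more patients enrol before a death counts, and to 0.06 if 15 do.

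**3. Route (a), the mortality limit.** This assumes that the 15% limit is read as an observed proportion in the same 39 patients.

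- Without the shift the mean risk is (8 + 15 + 30)/3 = 17.7%.
- Passing means at most 5 deaths (5/39 = 12.8%; 6/39 = 15.4%), with probability about 0.29.
- With the shift, mean risk falls to about 15-16% and the chance of passing rises to about 43-47%. It is 49% if every death is known at once, and lower with slower reporting or faster accrual.

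**4. Route (b), if pre-treatment deaths are left out.** Assumptions: constant hazard and the lags shown; the documents give no lag. Hazard = -ln(0.49)/12 = 0.0594 per month. Apparent 1-year survival = 0.49/exp(-0.0594 × lag in months).

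| Lag | Months | Apparent survival | P(25 or more of 39) |
|---|---|---|---|
| 2 weeks | 0.46 | 50.4% | 0.06 |
| 4 weeks | 0.92 | 51.8% | 0.08 |
| 8 weeks | 1.84 | 54.7% | 0.15 |

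**5. Route (b), planning failures.** If a fraction f fails planning and has survival D points worse, the rest have 0.49 + f × D. For f of 5-20% and D of 10-20 points this is 49.5-53.0%, with error 0.048-0.109. The documents do not say that such patients do worse. These patients are treated at another schedule, so this is selection and not immortal time.

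**The case against.** **A dose-specific population is a legitimate, declared choice.** The protocol names it in two places. Making all enrolled patients primary would pool three fractionations and answer a different question. This stands, and the fix respects it.

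**Much is already reported.** Data safety monitoring promises results for all patients and by dose level, and the Fig. 1 legend says analysis is stratified by ILD severity. A reader would see the mix. This lowers the severity, but the test and the worthwhile rule remain tied to the selected set.

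**The sizes rest on assumed inputs.** This stands: the cohort gradients, the lag and the speed at which deaths become known are not in the documents. Eligibility requires life expectancy above 6 months, so early hazard is probably below average and route (b) smaller than tabulated.

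Three stronger readings are tempting but not supported:

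- A reader might infer that cohorts with early deaths are removed. Only further patients of such a cohort stop counting; those already treated at the target dose remain.
- A reader might infer that the protocol drops pre-treatment deaths. No passage says so. It is one reading of the wording, and the enrolment flowchart (Additional file 5) is not shown.
- A reader might take the chance that at least one of three cohorts de-escalates, 1 - (1 - 0.283)³ = 63% at 15% risk in each, as the scale of the bias. That scenario has equal risks, and with equal cohort survival the simulated error stays at 0.04.

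**Conclusion.** The concern holds in a limited form and should be fixed. The primary set is defined by post-enrolment events, the clock starts at enrolment, and the pooled result is carried over to the whole ILD population.

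Route (a) is a case-mix shift only. It produces no survival bias if groups have equal survival. Over the gradients examined, the error runs from about 0.04 to 0.11, against a nominal 0.042, and the chance of meeting the mortality limit rises from about 30% to 43-47% at grade 5 risks of 8/15/30%. The ILD severity section makes some gradient likely, but its size is unknown. Subtype triggers, which were not modelled, are a further route to the same shift.

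For route (b), exclusion of planning failures is explicit. Exclusion of pre-treatment deaths is an ambiguity; if it applies, the error is about 0.06 to 0.15 for lags of 2 to 8 weeks under constant hazard, and less if early hazard is low.

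**What to change.** Keep the 50 Gy in 5 fractions set as the dose-specific primary population, and make these changes:

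1. **Align clock and set.** Either start overall survival at the first fraction, or keep the enrolment clock and retain every enrolled patient planned for 50 Gy in 5 fractions, including those who die before treatment. If the clock moves, state what time origin the historical 49% is taken to have.
2. **Limit the claim.** Confine any statement that SABR is worthwhile to cohorts and subtypes that were not de-escalated.
3. **Name two supportive analyses.** First, 12-month survival from enrolment in all enrolled eligible patients. Second, survival and treatment-related mortality in the primary set, standardised to the ILD-GAP mix of all enrolled patients.

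The cost is a change of wording and two extra estimates; no treatment or monitoring rule changes. The price is a narrower claim and wider intervals for the standardised estimate, which may be unstable if a de-escalated cohort contributes only a handful of patients at the target dose.
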